# Remote ischemic conditioning for the prevention of stroke-associated pneumonia (RICA-2): protocol for a multicenter, prospective, randomized, double-blind, sham-controlled phase III trial

**DOI:** 10.1186/s13063-025-09140-x

**Published:** 2025-10-16

**Keywords:** Remote ischemic conditioning, Acute ischemic stroke, Stroke-associated pneumonia, Clinical trial, Protocol

## Abstract

**Background:**

Stroke-associated pneumonia (SAP) is one of the most common complications in acute ischemic stroke (AIS) patients, affecting 8.5% to nearly 30% of cases and significantly impacting both mortality and long-term survival. As it is closely related to worse outcome, exploring effective preventive strategies, such as remote ischemic conditioning (RIC), is essential for reducing SAP incidence and improving patient outcomes. This study aims to compare the efficacy and safety of RIC for preventing SAP in patients with ischemic stroke within 24 h of symptom onset.

**Methods and design:**

RICA-2 is a multicenter, randomized, double-blind, parallel-controlled, phase III clinical trial in China. This study will enroll an estimated 1650 patients aged ≥ 18 years within 24 h after AIS symptom onset, with National Institutes of Health Stroke Scale ⩾ 4. The patients will be randomly assigned to RIC or Sham-RIC (1:1) and will be treated with cuff inflation at 200 mmHg or 60 mmHg, respectively. This procedure will be administered twice daily for seven consecutive days. The primary efficacy endpoint is SAP incidence rate. Safety incidence will be recorded and reported.

**Discussion:**

RIC has broad clinical application prospects and may play a preventive role in stroke-related pneumonia. RICA-2 is designed to verify whether RIC treatment can serve as an adjuvant therapy for preventing stroke-associated pneumonia and to identify safety concerns.

**Trial registration:**

ClinicalTrials.gov NCT05982015. Registered on January 22, 2024.

**Supplementary Information:**

The online version contains supplementary material available at 10.1186/s13063-025-09140-x.

## Introduction and rationale

Stroke-associated pneumonia (SAP) is one of the most common complications after stroke [1]. SAP is strongly associated with increased mortality rates in stroke patients [2], significantly increasing the risk of death up to 3 years poststroke [3]. During a stroke, local inflammatory activity intensifies while systemic immune function decreases, resulting in immunosuppression, which is a primary independent risk factor for SAP in stroke patients [4]. Given the substantial impact of infections on functional recovery, numerous trials have explored the efficacy of prophylactic antibiotics in stroke care. However, these studies have shown considerable heterogeneity in design, antibiotic type, and measured outcomes, limiting their generalizability [5], as seen in trials such as the Preventive Antibiotics in Stroke Study and STROKE Infection Prevention Study [6, 7]. Therefore, novel treatments aimed at reducing SAP and improving recovery outcomes in stroke patients are urgently needed [8].

Remote ischemic conditioning (RIC) has emerged as a promising nonpharmacological intervention to protect distant organs by inducing periodic ischemia and reperfusion in the limbs. Studies suggest that RIC activates endogenous protective mechanisms, protecting remote organs [9, 10]. In an experimental ischemia–reperfusion model, RIC has been shown to reduce cerebral ischemia–reperfusion injury, inflammation, brain edema, and neuronal apoptosis [11]. Whether RIC can be adopted as an effective treatment to decrease SAP occurrence in patients with AIS remains unclear.

Therefore, this study aimed to evaluate the efficacy and safety of RIC in preventing SAP in patients with ischemic stroke. This multicenter, double-blind, randomized, sham-controlled phase III trial is designed to provide robust evidence on a novel prevention method for SAP, as well as the potential benefits of RIC.

## Methods

### Design

This study is a multicenter, randomized, double-blind, sham-controlled phase III clinical trial (http://www.clinicaltrials.gov NCT05982015) in China and approved by the Ethics Committee of Xuanwu Hospital of Capital Medical University and other cooperative hospitals. The design is shown in Fig. 1. Patients will be subjected to head computed tomography (CT) or magnetic resonance imaging (MRI) before randomization to identify patients with ischemic stroke. All the subjects received optimal medical therapy on the basis of the 2018 clinical guidelines for AIS [12]. Before each participant is enrolled, the researcher is responsible for providing a comprehensive overview of the study’s purpose, procedures, and potential risks to the patient or his or her representative. The participants or their legally authorized representative signed a written informed consent form and were informed of their right to withdraw from the study at any time.

**Fig. 1 Fig1:**
[figure not shown]
Study design

### Patient population

A total of 1650 patients with acute AIS within 24 h of onset were recruited from approximately 80 medical centers in China according to the inclusion and exclusion criteria in Table 1.

**Table 1 Tab1:** Patient selection criteria

**Inclusion criteria**
• Age ≥ 18 years old
• Diagnosis of acute ischemic stroke
• RIC or Sham-RIC can be treated within 24 h after stroke onset
• NIHSS score ≥ 4
• Subject or his or her legally authorized representative was able to provide informed consent
**Exclusion criteria**
• During the screening period, body temperature ≥ 38 °C
• Evidence of lung infection, urinary tract infection, or other infectious diseasesduring the screening period
• Expected lifespan less than 7 days
• Mechanical ventilation is expected to be required within 7 days
• Anti-infective drugs were used within 7 days prior to stroke
• Uncontrolled hypertension with medication (defined as systolic blood pressure ≥ 200 mmHg and/or diastolic blood pressure ≥ 110 mmHg)
• There are contraindications for remote ischemic conditioning (such as skin and soft tissue injury, fractures, and peripheral arterial disease in the upper limbs)
• History of autoimmune disease or malignancies
• Use of immunosuppressive drug within the preceding 3 months
• Pregnant or lactating, or pregnancy test positive
• Current participation in another investigational trial
• Other conditions are not suitable for this trial as evaluated by researchers

*RIC* Remote ischemic conditioning. *Sham-RIC *Sham remote ischemic conditioning, *NIHSS* National Institutes of Health Stroke Scale

### Randomization

Randomization will occur after written informed consent is obtained from the patient or his or her guardian. Following successful screening of participants, patients will be randomly assigned to either the RIC group or the Sham-RIC group at a 1:1 ratio via randomized blocks (4, 6, and 8) stratified by age (≤ 70 or > 70 years old), stroke severity (NIHSS scores between 4 and 20 years or higher than 20), and sex (male or female). A central network randomization system will generate random code. Neither patients nor researchers will have information on the group allocation. Both RIC and Sham-RIC will be administered via equipment with the same appearance but with different pressure settings for the two treatment regimens. Additionally, consecutive enrolled subjects will not be placed in the same ward for this study.

At the end of this study, the subjects were asked several questions, as shown in Table 2, to investigate unblinding situations. Unblinding will only be allowed if a participant’s health is at risk and the attending physician deems it necessary. Unblinding must be approved by the principal investigator and documented.

**Table 2 Tab2:**
[figure not shown]
Blinded survey

### Baseline measurements

In addition to confirming eligibility for AIS, a comprehensive baseline assessment will be conducted prior to randomization. This assessment will encompass several key variables, including demographic characteristics, clinical and medical history, physical examination findings, vital signs, smoking and alcohol consumption status, and medication usage within 1 week prior to admission. Additionally, laboratory examinations, neuroimaging, and chest imaging, including CT or chest X-ray scans, will also be performed. Furthermore, the assessment will utilize standardized scales such as the National Institutes of Health Stroke Scale (NIHSS), the modified Rankin scale (mRS), the self-rating depression scale (SDS), the generalized anxiety disorder scale (GAD-7), and a swallowing function assessment.

### Intervention and assessment

Eligible patients will be randomly assigned to either the RIC group or the Sham-RIC group. The RIC procedure consisted of 5 cycles of inflation to a pressure of 200 mmHg (RIC group) or 60 mmHg (Sham-RIC group) and deflation for 5 min alternately within 1 h of enrollment performed on the upper arm by an electric autocontrolled device with cuff (patent number ZL201420846209.5, China); the total process lasted 45 min. The Sham-RIC did not result in upper limb ischemia. All patients will receive optimal medical treatment and care from local medical practices throughout the study. The numbers of RIC treatment will be recorded by the study nurse and signed their names per time. The electronic data collection system will send message to the researcher to remind them to visit patients.

Adherence is defined as completion of at least 10 out of the 14 scheduled RIC sessions (≥ 70%). Participants completing fewer than 10 sessions will be considered non-adherent. In such cases, study staff will promptly contact the participant to determine the reason for non-adherence and provide necessary support. When necessary, additional instruction or clarification will be offered to reinforce the importance of RIC and ensure correct implementation. Regular follow-up communication will be maintained to encourage continued participation and improve adherence.

The research period spans approximately 2 years. Research protocol version 3.0, version date July 19, 2023, recruitment date January 22, 2024, recruitment completed on September 12, 2024. The final follow-up period for the subject is expected to be completed on December 12 (± 7 days), 2024. Follow-up visits will be scheduled at each research center on days 1, 3, 7, and 90 after the initiation of treatment, as well as at the conclusion of the study. The details are outlined in Table 3.

**Table 3 Tab3:**
[figure not shown]
Schedule of activities and assessments

^1^For all enrolled cases, head CT or head MRI examination will be the first choice before randomization. Vital signs are related to blood pressure, heart rate, body temperature, and breathing rate. Physical examination includes weight, height, and limb examination; laboratory examination: white blood cell, red blood cell, platelet, hemoglobin, neutrophil, monocyte, and lymphocyte counts and percentages, C-reactive protein, high-sensitivity C-reactive protein, alanine aminotransferase, aspartate aminotransferase, creatinine, glucose, total cholesterol, triglycerides, high-density lipoprotein, low-density lipoprotein, homocysteine, lipoprotein(a), D-dimer, fibrinogen, and uric acid, *SAP* Stroke-associated pneumonia, *AE* Adverse event, *CT* Computed tomography, *EQ-5D-5L* EuroQoL 5-Dimensions 5-Level questionnaire, *MRI* Magnetic resonance imaging, *mRS* modified Rankin scale, *NIHSS* National Institutes of Health Stroke Scale; *SAE*, serious adverse event

### Outcomes

The primary efficacy endpoint is the incidence of SAP within 7 days of intervention after randomization. The details of the SAP diagnostic criteria [13] are presented in Table 4. The secondary endpoints were as follows: diagnosis of pneumonia by clinical doctors within 7 days; diagnosis of pneumonia by clinical doctors between 8 and 90 days; mRS score of 0–1 ratio on day 90; mRS score of 0–2 ratio on day 90; distribution of mRS scores on day 90; EuroQoL 5-Dimensions 5-Level questionnaire (EQ-5D-5L) score on day 90; NIHSS scores at 24 h after onset; NIHSS scores at day 7; incidence of urinary tract infection within 7 days; incidence of all infections within 7 days; all-cause mortality within 90 days; and total inpatient days. The incidence of adverse events was recorded and reported.

**Table 4 Tab4:** Suggested diagnostic criteria for definite and probable SAP in non-ventilated patients, based on CDC guidelines

At least one of the following criteria:
1. Fever (beyond 38 °C) with no other recognized cause
2. Leukopenia (lower than 4000 WBC/mm^3^) or leukocytosis (beyond 12,000 WBC/mm^3^)
3. For adults aged beyond 70 years, altered mental status with no other recognized causeAnd at least two of the following symptoms need to be observed:New onset of purulent sputum, a change in sputum character over 24 h, or increased respiratory secretions, or increased suctioning requirementsNew onset or worsening cough, dyspnea, or tachypnea (respiratory rate > 25/min) rales, crackles, or bronchial breath soundsWorsening gas exchange (e.g., O_2_ desaturation such as PaO_2_/FiO_2_ lower than 240, or increased oxygen requirements)And at least two serial chest radiographs must show at least one of the following:New or progressive and persistent infiltrate, consolidation, or cavitationOne definitive chest radiograph is acceptable in patients without underlying pulmonary or cardiac disease

Legend: Definite SAP: all CDC criteria are fulfilled, including diagnostic changes on at least one chest x-ray. CDC refers to the Centers for Disease Control and Prevention; *FiO*_*2*_ Fraction of inspired oxygen, *PaO*_*2*_ Partial pressure of oxygen, *SAP* Stroke-associated pneumonia, and *WBC* White blood cell count

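### The early NIHSS endpoint is timed from stroke onset while entry runs to 24 h and visits count from treatment start, so exposure at the assessment varies and can fall to about zero

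*Protocol article*

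**What the plan says.** Three clocks appear in the protocol article.

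- **Endpoint (Outcomes).** One of the twelve secondary endpoints is "NIHSS scores at 24 h after onset". The other NIHSS endpoint is at day 7.
- **Entry (Table 1, Inclusion criteria).** Eligibility requires that "RIC or Sham-RIC can be treated within 24 h after stroke onset". The Abstract words the limit as an enrolment window, "within 24 h after AIS symptom onset".
- **Visits (Intervention and assessment).** "Follow-up visits will be scheduled at each research center on days 1, 3, 7, and 90 after the initiation of treatment".

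The same section places the first session "deflation for 5 min alternately within 1 h of enrollment" and says that "the total process lasted 45 min". On frequency, the Abstract says: "This procedure will be administered twice daily for seven consecutive days". Under Baseline measurements, "a comprehensive baseline assessment will be conducted prior to randomization", and this includes the NIHSS.

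Under Statistical analysis, continuous secondary endpoints go into linear regression adjusted for the stratification factors. The Randomization section defines the NIHSS factor as 4 to 20 versus above 20. Secondary outcomes are described as exploratory and analysed on complete data.

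**The concern.** The assessment time and the entry window close at the same moment, 24 h after onset. How much treatment a patient has had by then depends on how late treatment began, and at the limit it is none. For such patients the value largely repeats the NIHSS taken before randomisation and can carry little or no treatment effect.

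The endpoint's clock also differs from the visit clock. For a patient first treated at 18 h, the endpoint as worded falls 6 h after treatment start. If day 1 means 24 h after treatment start, that visit falls 18 + 24 = 42 h after onset. These are different quantities, and the readable text does not say which one the endpoint uses.

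At stake is the reading of the only early neurological endpoint. If it shows no difference, the reader cannot tell an absent early effect from too little exposure.

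**Working it through.** The plan gives no figure for this endpoint, so there is none to reproduce. The sample size calculation concerns the primary endpoint only and plays no part here.

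**Inputs.** Assessment at 24 h after onset (Outcomes); first session up to 24 h after onset (Table 1); session length 45 min = 0.75 h and first session within 1 h of enrolment (Intervention and assessment); enrolment up to 24 h after onset (Abstract); 14 scheduled sessions, two a day for seven days.

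**Step 1: exposure for one patient.** With t the start of the first session in hours after onset:

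- exposure from session start = 24 - t
- time since the end of the first session = 24 - (t + 0.75)

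| t (h) | 24 - t (h) | 24 - (t + 0.75) (h) |
|---|---|---|
| 6 | 18 | 17.25 |
| 12 | 12 | 11.25 |
| 18 | 6 | 5.25 |
| 22 | 2 | 1.25 |
| 23.25 | 0.75 | 0 |
| 24 | 0 | -0.75 |

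A start after 23.25 h means that no session is complete at the assessment. A start at 24 h, the Table 1 limit, puts the assessment at the moment the first session begins.

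**Step 2: can the assessment come before the first session?** Not under Table 1, where t is at most 24. It can only if the Abstract's window is read as enrolment up to 24 h and the 1 h allowance is added. Then t reaches 24 + 1 = 25, exposure is 24 - 25 = -1 h, and the assessment precedes the session by up to 1 h.

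**Step 3: spread over patients.** The documents give no distribution of start times. As an assumption, take starts uniform from a lower bound a up to 24 h:

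- mean exposure = (24 - a)/2
- share with no completed session = 0.75/(24 - a)
- share with less than 6 h since the end of the first session (t > 17.25) = 6.75/(24 - a)
- share with at most one completed session, if sessions are 12 h apart (a second assumption; the second session ends by 24 h only when t ≤ 11.25) = 12.75/(24 - a), capped at 1

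| a (h) | Mean exposure (h) | No completed session | Less than 6 h since session end | At most one of 14 sessions |
|---|---|---|---|---|
| 0 | 12 | 3.1% | 28% | 53% |
| 3 | 10.5 | 3.6% | 32% | 61% |
| 6 | 9 | 4.2% | 38% | 71% |
| 12 | 6 | 6.3% | 56% | 100% |

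**Step 4: comparison with a treatment anchor.** At 24 h after treatment start, every patient would be assessed 24 - 0.75 = 23.25 h after the end of the first session, whatever the value of t.

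**The case against.** The strongest reply is that little depends on this endpoint. It is one of twelve secondary endpoints that the article itself calls exploratory. Randomisation balances time from onset to treatment in expectation, so the comparison between arms stays valid. The primary endpoint, sample size and safety reporting are untouched, and NIHSS is measured again at day 7. All of this stands, and it limits the point to lost sensitivity and an unclear time point.

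Four stronger readings are tempting, and the documents do not support them.

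- **The effect is diluted by half.** That needs both a uniform start time from 0 h and an effect growing linearly over 24 h. The documents give neither.
- **The assessment precedes treatment.** Under Table 1 it can coincide with the first session but not precede it. Strict precedence needs the combination in Step 2. Under the assumptions in Step 3, only about 3% to 6% of patients would lack a completed session, so the nearly-baseline description fits a tail.
- **No visit matches this endpoint, and sites will have mixed two time points.** The schedule in Table 3 is not shown here and may list this NIHSS separately, so neither statement can be checked.
- **The baseline score is ignored.** The models already adjust for NIHSS as a stratification factor. What is unclear is whether it enters as the score or only as the two categories.

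A last objection concerns timing. Intervention and assessment reports recruitment completed in September 2024 with last follow-up expected that December, and the article appeared in October 2025. The values have presumably been collected, so a new definition cannot change what was measured. This also stands and shapes the fix.

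**Conclusion.** The point holds as a mismatch of time anchors. Exposure at the assessment is 24 - t hours and falls to zero at the Table 1 limit, and nothing in the readable text re-anchors the endpoint. This follows from the article's own windows without further assumption. Condensing a fuller protocol does not explain it, because the article states the anchor outright.

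The consequence is reduced sensitivity to an early effect and exposure that differs between patients. It is not bias between arms. The size depends on unreported start times: mean exposure is 12, 10.5, 9 or 6 h if starts are uniform from 0, 3, 6 or 12 h. No percentage loss of effect can be stated. The anchor conflict is certain; its practical weight is modest.

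**What to change.** 1. **Reconcile the anchors.** Establish from the full schedule and the data when this NIHSS was taken. If it was recorded at the day 1 visit, reword the endpoint as NIHSS at that visit, counted from treatment start, and document the change before unblinding. The article does not say whether unblinding has taken place. If it has, keep the prespecified wording and label any re-anchored analysis as post hoc.
2. **If the values truly are from 24 h after onset**, keep the endpoint. Report the distribution of time from first session to assessment by arm, and say in advance that a null result would be weak evidence against an early effect.
3. **In either case**, put the baseline NIHSS score into the linear model as a continuous covariate, and not only the 4 to 20 versus above 20 stratum. The score is already collected.
4. **Entry wording.** The Abstract limits enrolment to 24 h while Table 1 limits treatment to 24 h. With the 1 h allowance the two can differ, so they should be reconciled.

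The cost is one documented wording change and a small amount of extra analysis, with no new data if session and assessment times were recorded.

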### Sample size

On the basis of previous studies [14] and a recent survey from Xuanwu Hospital, the estimated incidence of SAP in patients with AIS within 24 h of onset is 17%. The sample size calculation assumes that RIC will reduce the SAP rate from 17.0% to 11.9%. With a sample size of 1486 across both groups, the study will have 80% power to detect a difference in SAP incidence between the Sham-RIC and RIC groups at a two-sided significance level of 0.05. While we anticipate that all (or at least a very high proportion) of the enrolled patients will be evaluable at the end of the study, we intend to recruit 875 patients per treatment group, totaling 1650 patients for this study.

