## Discussion

In our previous pilot clinical trial investigating the safety and efficacy of remote ischemic conditioning for SAP, 19 patients with AIS onset within 48 h were randomly assigned to the RIC group (six consecutive days, twice daily), whereas 22 patients were assigned to the control group. The results of this study showed that RIC was safe among patients with AIS. Although the difference was not statistically significant in either univariate or multivariate analyses, the incidence of SAP was lower in the RIC group (10.5%) than in the control group (27.3%) [15]. The lack of statistical significance may be attributed to the small sample size, limiting the power to detect differences between groups, and recent evidence suggests that the peak of apoptosis and immune suppression following stroke may occur within the first 24 h [16], indicating that earlier prevention might be more beneficial among these patients. Therefore, we aimed to conduct a fully powered clinical trial with adjusted inclusion and exclusion criteria to investigate the efficacy of RIC in preventing SAP in AIS patients within 24 h of symptom onset following randomization. We hypothesize that 7 days of RIC will reduce the relative risk of SAP by 30%.

We implemented several adjustments to address the limitations identified in the previous study [15]. The inclusion criteria were refined to ensure that the treatment window was within 24 h of stroke onset, as this period is critical for effectively reducing apoptosis and modulating immune responses. Since the sample size calculation was based on previous studies [14], clinical expertise, and prior surveys on SAP incidence at Xuanwu Hospital of Capital Medical University and our participant selection criteria are relatively broad, we anticipate few practical challenges in recruiting a sufficient number of patients. An important advantage of our approach is that the results of our trial can be generalized to a wider population of stroke patients. Additionally, at the end of the study, we used a method from previous research [17] and contacted the participants, asking them about their knowledge of group allocation by answering the questions in Table 1. This upcoming trial is anticipated to conclude in the second quarter of 2025.

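### The recruitment target does not add up: 875 per group at 1:1 is 1750, not the stated 1650, which is 825 per group

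*Protocol article*

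**What the plan says.** The Sample size section of the protocol article starts from a control-group assumption, "the estimated incidence of SAP in patients with AIS within 24 h of onset is 17" per cent, and "assumes that RIC will reduce the SAP rate from 17.0% to 11.9" per cent. The Discussion gives the same effect in relative terms: "We hypothesize that 7 days of RIC will reduce the relative risk of SAP by 30" per cent. The powered size follows: "With a sample size of 1486 across both groups", "the study will have 80% power to detect a difference in SAP incidence", at a two-sided level of 0.05.

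The section then moves from evaluable to recruited patients. It expects nearly everyone to be evaluable but still plans to enrol more than 1486: "we intend to recruit 875 patients per treatment group, totaling 1650 patients for this study".

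The total is given in two other places. The abstract, under Methods and design, says "This study will enroll an estimated 1650 patients", and Patient population says "A total of 1650 patients with acute AIS". The figure of 875 per group appears nowhere else. The Randomization section fixes allocation at 1:1 between two groups. No numerical rate of dropout or non-evaluability is stated.

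**The concern.** Two groups of 875 make 1750. A total of 1650 at 1:1 makes 825 per group. The sentence that fixes the size of the trial therefore contains two figures that exclude each other.

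The planned sample size is a figure that the results paper and later reviews will quote and against which completed enrolment will be compared. The Statistical analysis section says that no interim analysis is planned, so this target is the only numerical end point for enrolment that the article gives. As printed, it can be read in two ways, 100 patients apart, and each reading implies a different margin for patients without an evaluable primary outcome.

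**Working it through.** **Inputs.** Control rate 17.0%, RIC rate 11.9%, two-sided alpha 0.05, power 80%, 1486 evaluable, 875 per group, 1650 in total (all from Sample size); 1:1 allocation (Randomization); 30% relative reduction (Discussion). The effect sizes agree: 1 − 11.9/17.0 = 0.30.

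**Step 1: reproduce the powered size.** Normal approximation for two proportions with unpooled variance:

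n per group = (1.96 + 0.8416)² × (0.17 × 0.83 + 0.119 × 0.881) / (0.17 − 0.119)²
= 7.849 × (0.1411 + 0.1048) / 0.002601
= 742.2, rounded up to 743.

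2 × 743 = 1486, exactly the stated figure. The pooled-variance version gives 745 per group and 1490 in total. The powered size is sound, so the fault lies only in the recruitment sentence.

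**Step 2: add up the recruitment target.**
- 2 × 875 = 1750, and 1750 − 1650 = 100 patients (100/1650 = 6.1%).
- 1650 / 2 = 825 per group.
- 875 in one group and 1650 in total would leave 775 in the other, which 1:1 allocation rules out.

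**Step 3: see what each figure would imply.**

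| Reading | Total | Surplus over 1486 | Share of total |
|---|---|---|---|
| 825 per group | 1650 | 164 | 164/1650 = 9.9% |
| 875 per group | 1750 | 264 | 264/1750 = 15.1% |

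Each figure resembles a conventional inflation. With 10% lost, 1486/0.90 = 1651, close to 1650. With 15% lost, 743/0.85 = 874.1, rounded up to 875 per group. The arithmetic alone therefore does not show which one was meant.

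**Step 4: power under each reading.** Power = Φ(0.051 / √(0.2459/n) − 1.96), with n observed outcomes per group:
- n = 743: Φ(0.843) = 80.0%
- n = 825: Φ(0.994) = 84.0%
- n = 875: Φ(1.082) = 86.0%

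The pooled-variance version gives 79.9%, 83.9% and 85.9%.

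**The case against.** The strongest reply is that this is a slip in one digit with no consequence. The total of 1750 is printed nowhere. Every printed total is 1650 and 875 occurs once, so the operative target is fairly clear. The powered size reproduces, both readings exceed it, and their power differs by about two percentage points. With no interim look, no information fraction depends on the total. Effect size, alpha and analysis model are untouched. All of this stands, and it limits the point to the recruitment sentence. It does not make that sentence correct: nothing in the article reconciles the two figures, and the choice of 825 remains an inference.

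Four stronger readings are tempting, and the document does not support them.

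- *The attrition allowance is wrong.* No allowance is stated, so none can be shown to be wrong. It is ambiguous, at 9.9% or 15.1%. An article may leave the rate to the full protocol; it matters here only because stating it would help to settle the conflict.
- *The article justifies its surplus by expecting nearly complete follow-up.* The clause is concessive: the surplus is planned despite that expectation, not because of it.
- *The intended allowance must be 10%, so 825 is proven.* A 15% allowance leads to 875 just as naturally. What favours 825 is the repetition of 1650.
- *Power is about 84% because multiple imputation brings all 1650 into the analysis.* The 84% needs 825 observed outcomes per group. Imputation does not in general restore the information in missing outcomes. If about 10% were missing, about 1486 outcomes would be observed and power would be near 80%, barring strong auxiliary predictors.

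Nor can a reader infer that the trial under- or over-recruited. The article does not report an enrolment count separately from the target.

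**Conclusion.** The concern holds for the recruitment target alone. As written, 875 per group and 1650 in total are incompatible under 1:1 allocation, by 50 patients per group and 100 overall. That is an error in a figure the trial relies on, and it should be corrected. The likelier intent is 825 per group, but this needs the sponsor's confirmation.

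The 80% power claim stands. It rests on 1486 evaluable patients, which reproduces exactly with unpooled variance, and it survives unless losses exceed about 9.9% (if 1650) or 15.1% (if 1750). These statements take the stated 17.0% and 11.9% as given. Confidence is high for the mismatch and lower for which figure is the slip.

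**What to change.** Correct the recruitment sentence in the Sample size section so that it

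1. gives one consistent pair of figures: 825 per group and 1650 in total if the sponsor confirms 1650 as the approved target; if the approved figure is 875 per group, the total becomes 1750, and the abstract and Patient population must change as well;
2. states the non-evaluable proportion actually assumed, taken from the full protocol and not worked back from the totals;
3. says that 80% power refers to 1486 evaluable patients (743 per group).

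If power at the full target is quoted as well, it should read about 84% for 1650, or about 86% for 1750, on the condition that every primary outcome is observed. It should not be credited to multiple imputation.

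If 1650 is confirmed, the cost is one sentence and a check against the approved protocol. The design does not change and no extra patients are needed.
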